### Study design

2.1

Through a randomized, double-blind, and placebo-controlled clinical trial, we will investigate the curative efficacy and safety of DLT in patients with SAP. The trial will include a 1-week screening period and a 4-week treatment period. We plan to enroll 76 participants, who will be allocated randomly in a 1:1 ratio by a central randomization system (CRS) into the intervention group and the control group. Following the original medication regimen, participants will take DLT or placebo 3 times per day. This trial has already been registered at the Chinese Clinical Trial Registry on December 9, 2019 (ChiCTR-1900028068), following the principles of the Declaration of Helsinki and Good Clinical Practice guidelines. We will strictly follow the Consolidated Standards of Reporting Trials (CONSORT 2017)^[26]^ and the Standard Protocol Items: Recommendations for Interventional Trials (SPIRIT 2013)^[27]^ for the research design. A flow diagram illustrating our study design is presented in Figure 1.

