### Safety outcomes

2.9

The safety outcomes include vital signs and laboratory examinations, all of which will be performed in weeks 0 and 4. Vital signs include body temperature, respiration rate, heart rate, and blood pressure. Laboratory tests—ECG and blood routine, urine routine, and stool routine tests—will be used to evaluate occult blood, liver function (alanine aminotransferase, aspartate aminotransferase, γ-glutamyl transpeptidase, total bilirubin, and alkaline phosphatase levels), and renal function (urea nitrogen and Crea levels). The severity and incidence of AEs or reactions will be recorded in detail.

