### Statistical analysis

2.16

Statistical analyses consist of 3 parts—baseline comparability analysis, efficacy analysis, and security analysis. An independent statistician will be in charge of the analyses, and Statistical Analysis System (version 9.2) will be used. All tests are 2-sided, and *P* < .05 is considered to indicate statistical significance. According to the intention-to-treat principle,^[32]^ there will be 3 analysis sets: the full analysis set, the per-protocol analysis set, and the safety analysis set. Participants who insist in taking medication for 2 weeks will be involved in the full analysis set group; if a critical variable is missing in any given case, the statistician will consider the last observation result as the final data. Patients who conform to the treatment plan will be included in the per-protocol analysis set group. The Mantel–Haenszel Chi-squared test and analysis of covariance will be conducted in the case of important baseline non-comparability. Normally distributed quantitative data will be presented as mean ± standard deviation and analyzed by Student *t* test. Non-normally distributed quantitative data will be presented as median and interquartile range and analyzed by the Kruskal–Wallis test. Ordinal data, like ECG efficacy, will be analyzed by the Kruskal–Wallis test. Qualitative data will be presented as percentage and rate and analyzed by the Chi-square test and Fisher exact test. The paired Student *t* test will be used to analyze significant differences between pre- and post-treatment. Moreover, subgroup analysis will be conducted according to gender, age, and complications to explore the internal consistency of the conclusions. For the safety analysis, the statistician will adopt the safety analysis set to evaluate the incidence rate of AEs and the change of laboratory indices. Both AEs and laboratory indices are described in lists and analyzed by the chi-square test or Student *t* test.

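### The only between-arm safety methods are chi-square and t tests at P < .05, which at 30 to 38 per arm have low power for a doubling or tripling of AE incidence; estimates with confidence intervals should carry the safety summary

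*Protocol article*

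**What the plan says.** Safety is a stated aim. Under Study design (2.1) the article writes "we will investigate the curative efficacy and safety of DLT in patients with SAP", and the abstract and Introduction also name safety beside efficacy.

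Safety outcomes (2.9) lists what is measured: "The safety outcomes include vital signs and laboratory examinations, all of which will be performed in weeks 0 and 4". That section also has AE severity and incidence recorded.

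Statistical analysis (2.16) makes safety one of three parts of the analysis. It says that "the statistician will adopt the safety analysis set to evaluate the incidence rate of AEs and the change of laboratory indices", and then that "Both AEs and laboratory indices are described in lists and analyzed by the chi-square test or Student *t* test". The general rule is "All tests are 2-sided, and *P* < .05 is considered to indicate statistical significance". For qualitative data in general, the section has them "analyzed by the Chi-square test and Fisher exact test"; the safety sentence itself names only chi-square and Student t.

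Elsewhere, Adverse events (2.12) has each AE recorded with its timing, severity, duration, measures taken and outcome, and graded for causality on five levels. Section 2.6 discontinues the trial if emergency events exceed 20% of the sample. Sample size estimation (2.11) uses angina frequency alone. No interval estimate or margin is named for safety.

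**The concern.** The lists and causality grades describe single cases, and the 20% rule looks at the sample as a whole. None of them compares Danlou tablet with placebo; that task falls to the significance tests. In a trial of this size, a non-significant AE test is the likely result even when the true incidence on active treatment is two or three times that on placebo.

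The laboratory test has a further weakness. Harm to the liver may appear as a large rise in a few participants and not as a shift of the whole group. Such rises raise the standard deviation along with the mean, so a test on means responds little.

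At stake is what the report can say about safety. A P value above .05 does not show how large an excess of harm the data still allow. An interval does.

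**Working it through.** **Arm size.** From 2.11: 30 per group with 20% dropout gives 30/(1 − 0.2) = 37.5, so 38 per arm and 76 in total. This reproduces the plan's total. The article does not define who belongs to the safety set, so 30 to 38 per arm is used as the range. (The 27 per group behind the 30 does not reproduce: with pooled SD √((0.45² + 1.03²)/2) = 0.795 and difference 0.65, a two-sided 5% test with 90% power needs 32 by the normal formula or 33 by t. A one-sided 5% test gives 26 or 27. That is a separate matter and does not affect this point.)

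**AE incidence.** The documents give no AE rates, so the rates are assumed and shown as a range. Power is the sum, over all pairs of counts (x, y), of the two binomial probabilities multiplied together, taken over the tables where two-sided P < .05.

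| Assumed placebo v DLT | Chi-square, n = 30 / 38 | Fisher, n = 30 / 38 |
|---|---|---|
| 5% v 10% | 11% / 14% | 2% / 4% |
| 5% v 15% | 26% / 33% | 9% / 16% |
| 5% v 20% | 45% / 55% | 24% / 38% |
| 5% v 25% | 63% / 74% | 44% / 61% |
| 5% v 30% | 78% / 87% | 63% / 79% |
| 10% v 20% | 19% / 24% | 10% / 15% |
| 10% v 30% | 50% / 61% | 37% / 50% |

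For 80% power by chi-square the trial would need 435 per arm for 5% v 10%, 141 for 5% v 15%, and 199 for 10% v 20%.

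**What an interval would show.** Take observed counts of 6/38 and 2/38. The difference is 0.158 − 0.053 = 0.105. The pooled rate is 8/76 = 0.105, so the standard error is √(0.105 × 0.895 × 2/38) = 0.070, z = 1.50 and chi-square P = 0.13 (Fisher 0.26). The Wilson limits are 0.074 to 0.304 and 0.015 to 0.173. Newcombe's interval is then:

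- lower: 0.105 − √((0.158 − 0.074)² + (0.173 − 0.053)²) = −0.041
- upper: 0.105 + √((0.304 − 0.158)² + (0.053 − 0.015)²) = 0.256

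The test reports no significant difference, while the data allow an excess of up to about 26 points. Likewise 3/38 against 0/38 gives chi-square P = 0.077, and 5/38 against 0/38 gives Fisher P = 0.054. Zero events of one type in an arm leaves a one-sided 95% upper bound of 1 − 0.05^(1/n): 7.6% at n = 38 and 9.5% at n = 30.

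**Laboratory means.** By the noncentral t distribution, with two-sided 5%, power for a 0.3-SD shift is 21% / 25% (n = 30 / 38) and for a 0.5-SD shift 48% / 58%. A shift of about 0.74 / 0.66 SD is needed for 80%.

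**A few large rises.** Assume 2 of 38 treated participants have ALT rises spread evenly over 80 to 160 U/L, with all other changes having mean 0 and SD 8. The treated mean is then about (2/38) × 120 = 6.3. Its variance is about (2/38)(120² + 80²/12) + (36/38)(8²) − 6.3² = 807, so the SD is 28.4. The t statistic is about 6.3/√((807 + 64)/38) = 1.3, against a critical value near 2.0. In 20,000 simulated trials Student t rejected in about 4%, no more than its nominal false-positive rate. With 3 such participants it rejected in about 16%. Moving to a rank test, as 2.16 allows for non-normal data, does not help: with 2 such participants it rejected in about 5% to 6%. A count above a limit shows the pattern directly.

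**The case against.** The strongest reply is that safety is not left to the tests. The same sentence puts the data in lists, the sentence before it has incidence evaluated, AEs are graded for severity and causality, serious reactions go to the Ethics Committee, and a 20% rule can end the trial. This is correct. A reader might infer that safety is judged by P values alone; the documents do not support that. What remains is narrower: none of these other elements compares the arms.

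A reader might also infer that a non-significant result is meant to count as proof of safety. No section says so, and 2.16 uses P < .05 only to define statistical significance. The point is what the tests could support, not what the authors have declared.

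Third, intervals and shift tables are often left to an analysis plan, and this is a condensed article. As an omission that would be no finding. But the article does fix a method for the safety comparison, and that choice can be improved. Naming these tests does not rule out intervals, which limits the weight of the point.

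Finally, low power for AEs is common in trials of this size, and sizing a trial on its primary outcome is normal. Both are true. They are reasons to report estimates, not to enlarge the trial.

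**Conclusion.** The point holds as a limited and cheaply remedied weakness. The stated between-arm safety tests have low power for a doubling or tripling of AE incidence: chi-square about 11% to 33% for 5% v 10% to 15% and 19% to 24% for 10% v 20%, with Fisher lower. They are not blind to harm in general. At 5% v 30% chi-square power is 78% to 87%, and at 38 per arm a 0.5-SD laboratory shift is found 58% of the time. A claim that most relevant harms would be missed therefore goes beyond the evidence, since it depends on AE rates that the documents do not give.

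The t test on mean laboratory change is close to uninformative when only two treated participants have large enzyme rises, and a rank test does no better.

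These figures rest on assumed AE rates, an assumed ALT pattern and a safety set of 30 to 38 per arm. The conclusion that a non-significant test here could not support a statement of safety does not depend on any one of those rates: the interval for 6/38 against 2/38 shows it directly.

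**What to change.** In 2.16, base the between-arm safety summary on estimates:

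- For AEs, report per arm the number of participants with at least one event, and the risk difference with its 95% confidence interval (Newcombe or exact).
- For laboratory indices, report shift tables from baseline to week 4 with counts above the upper limit of normal and, for ALT and AST, above the limit of 1.5 times that value already used in exclusion criterion (3). Add mean differences with 95% confidence intervals.
- Keep any P values as descriptive. State that P >= .05 is not evidence of safety and that the conclusion will quote the upper confidence limit.

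All of this uses data already collected before treatment and at week 4, so no extra participants or tests are needed. The cost is a few more tables and a more modest safety statement.

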## Discussion

3

This study is a WeChat-based block-randomized, double-blind, placebo-controlled, parallel-group clinical trial with the aim of investigating the efficacy of DLT on stable angina. DLT is a Chinese proprietary medicine for the treatment of “intermingled phlegm and blood stasis syndrome” in CAD. Nitroglycerin is usually applied for the acute phase of angina attacks, while long-acting nitrates and trimetazidine are utilized for the relatively stable period. DLT is taken 3 times per day, just like the latter. DLT has been proven effective in clinical trials, animal experiments, cell experiments, pharmacology studies, a metabolomics study, and a network pharmacology study. However, previous clinical studies of SAP may have limitations with respect to randomization, allocation concealment, blinding, and so on. Moreover, previous studies took therapeutic effective rates calculated from ECG efficacy, angina pectoris scores, and TCM syndrome scores as the primary outcomes. Different evaluation standards and study designs lead to greater systematic error. Therefore, we will choose angina frequency as the primary outcome for this study, as it quantitatively, objectively, and specifically reflects the treatment efficacy. Moreover, we will evaluate the degree of coronary artery stenosis by dual-source CT angiography and exclude patients who are diagnosed with myocardial infarction or have a stent implantation, in order to reduce selection bias and confounding factors and to ensure compliance with the patients’ inclusion criteria.

Currently, the combination of clinical medicine and Big Data is getting closer and closer, and WeChat could be considered as a “transfer station” of Big Data. WeChat is a smartphone application for instant messaging and transferring of files. During the COVID-19 pandemic, WeChat has become an indispensable tool for tracking travel records of people and inferring the development of new trends.^[33]^ Several studies have used WeChat to track the level of self-management of patients with hypertension,^[34]^ diabetes,^[35]^ and chronic obstructive pulmonary disease.^[36]^ Although WeChat has powerful functions and promising potential in the clinical field, no clinical research has been reported where the patients’ daily angina and medication were recorded using a questionnaire in WeChat. When participants fill in forms via WeChat, this can avoid forgetfulness and reduce the nonresponse bias and the measurement bias. In addition, it can prevent researchers from recording errors and falsifying data, which ensures the validity of results.

The limitations of this study can be summarized as follows.

(1)The trial is solely conducted in 1 hospital in Beijing, so the conclusions may not be generalizable globally.(2)This trial only observes the short-term effectiveness, the benefit of endpoint events should be further evaluated in the future studies.
